#### Study population

##### Recruitment

Active promotion about the park and the overall project will be communicated through the local councils’ various marketing platforms (social media, council’s website and Facebook, flyers, local newsletter). Potential participants for the face to face intercept interview will be recruited at the site. Information about the study will be provided to residents/visitors via verbal communication as well as via hard copies of the information sheet.

##### Inclusion criteria

For the observation data collection, all park visitors will be included in the data recording. For the face-to-face intercept survey, the following inclusion criteria will be applied: (1) older adults age 60 and over, (2) adults who are able to understand basic English and have conversational English.

##### Exclusion criteria

The following exclusion criteria will be applied: (1) participants who identify themselves as less than 60 years of age and (2) who are unable to understand basic conversational English.

##### Consent

Verbal consent will be required in order to participate in the face-to-face intercept survey. The research staff will explain the study and will seek verbal agreement/consent by the participant prior to commencing the survey. A hard copy of the information sheet will be available and will be offered to potential participants should they wish to read and or maintain a copy.

### Assessments

#### Outcome measures

##### Park observation and Seniors Exercise Park equipment usage

Observation of park and exercise equipment visitation and usage will take place prior to site construction (baseline) and at two time points: one month after the site is open for public and 12 months after baseline (Fig. 2). The inclusion of two measures post-refurbishment/construction allows time for residents to become aware of the new facilities [16]. The 12 months evaluation will take place at the same time of the year as the baseline assessments to account for potential seasonal effects.

Evaluation of usage and visitations will include periodic observation (using the System for Observing Play and Recreation in Communities (SOPARC)). The SOPARC is a reliable and feasible instrument for assessing physical activity and associated contextual data in community settings [17]. It is based on momentary time sampling techniques in which systematic and periodic scans of individuals and contextual factors within pre-determined target areas in parks are made. SOPARC was designed to obtain direct information on community park use, including relevant concurrent characteristics of parks and their users. It provides an assessment of park users’ physical activity levels, gender, activity modes/types, and estimated age and ethnicity groupings. Additionally, it provides information on individual park activity areas, such as their levels of accessibility, usability, supervision, and organization. As this study focuses on the usage of the Seniors Exercise Park, we will also collect additional data (not included in the original SOPARC protocol) by coding the interaction with the outdoor exercise equipment (i.e., ‘using equipment as intended’ or ‘playing/looking/sitting’ on the equipment) [18]. We will also note the number of people moving past the equipment area without interacting with the equipment. Each site will be divided into targeted areas to be scanned. Systematic scans will be conducted over a 7-day period (Monday-Sunday) with a total of 11 scans per day as follows (22 and 55 scans for weekend and weekdays respectively): every 30 min of all park visitors in the study area during early morning (07:00–08:30), mid-day (11:30–13:00) and late afternoon (16:00–18:30) [19].

##### Intercept survey with visitors

Face-to-face intercept surveys (10–15 min) will be conducted at baseline (prior to site construction) and at 12 months follow up during the periodic observation (SOPARC). Trained, clearly identifiable research assistants will approach park users in the specified target areas, and will explain the study and all ethical considerations, and invite participation. Potential participants will be approached and provided with a verbal explanation about the study. Interested participants will then be asked to provide verbal agreement (consent) to participate. If there is more than one person in the park, the research staff will aim to recruit an equal number of men and women. The participants will be eligible to complete only one intercept survey during each test period.

Intercept surveys will provide more in depth information about park users’ characteristics. The survey will include a set of questions across various domains similar to previous research [19, 20] as well as validated questionnaires (detailed below). The set of questions will include socio-economic and demographic characteristics of park users (e.g., age group, gender, if born in Australia, marital status), if they are local residents or visitors, motivation to use the exercise park, how often they visit the park, social connectedness/engagement with other people at the park, their general physical activity level and their leisure/recreation activity at the park, and general health and well being. The following validated questionnaires will be used as part of the survey:

*Self-reported physical activity*—will be measured using three questions from the Active Australia Survey (Australian Institute Of Health And Welfare, 2003 [21]), which assessed walking, moderate, and vigorous activity, plus an indicator of total activity. The Active Australia questions are valid and reliable and are recommended for use in Australian population-based research and will provide measures of time and frequency in light, moderate and vigorous physical activities [22]. The Active Australia questions can also provide a measure as an estimate of energy expenditure in MET-minutes per week.

*General wellbeing* will be assessed using the five-item World Health Organization (WHO-5) Wellbeing questionnaire [23, 24]. The WHO-5 measures psychological wellbeing and depressive symptoms using 5 simple questions. The raw score will be calculated to obtain a percentage score, which ranges from 0 representing the worst imaginable well-being and 100 representing the best imaginable well-being.

At the 12 months follow up intercept surveys will also include additional questions of park visitors’ participation in community events and general park attendance, perceptions of any changes to the park, usage of the exercise park equipment, and suggestions for future improvements to the park. Although the intercept survey will be completed anonymously, at the follow up time point (12 months), participants will be asked if they have completed it previously. The intercept surveys will be conducted at the same 7-day period of the SOPARC systematic scans.

##### Online access monitor platform – the ‘ENJOY-ME-APP’

An innovative e-monitor tracker platform (online Progressive Web Application—(‘*ENJOY-ME-APP’*)) will be designed and developed (Curve Tomorrow, Australia) to monitor the usage and access of the Seniors Exercise Park by visitors at each site. The online platform will include an online application incorporating specific exercise instructions, videos, and safety tips. Quick Response (QR) codes will be placed on the instructional signage and on the exercise equipment itself at each site. Visitors will be able to scan the QR code with their mobile phone. Each QR code will have a unique identification code linked to a specific site. Each time a QR code is being used it will be registered on a secured cloud platform. Scanning the QR code from a mobile device will direct the user to a url address (similar to accessing website from a mobile device). No personal identification, or any sensitive information, and or mobile numbers will be recorded.

Visitors will be able to access the online platform at the site, scan the specific QR code and access the relevant video and associated information. The e-monitor tracker platform will monitor overall use collecting information of usage such as frequency, time and date. Design and testing of the e-monitor tracker platform will be conducted in the first 3–6 months of the project.

##### Review and audit of physical activity programs

Information about the type and number of physical activity programs for older people using the Seniors Exercise Park will be provided by the council (from the Positive Ageing team or equivalent) to the research team. There may be different modes of delivery and or programs that will be delivered by the participating partners and/or their respective local health/leisure providers. This information will be collected in the last stage of each site between 15 and 18 months, see Fig. 2.

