## Abstract

**Background:**

Physical activity is important to maintain health in older age, with physical activity in the outdoors providing mental and physical health benefits for all age groups. One way by which older people can engage in physical activity in the outdoors is through using suitable age-friendly outdoor exercise equipment, the Seniors Exercise Park. The ENJOY MAP for HEALTH aims to evaluate the effect of the Seniors Exercise Park installation and associated capacity building activities on park visitation, park-based physical activity by older people and delivery of community physical activity programs.

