**Method:**

This study is a quasi-experimental (natural experiment) with pre and post study design evaluating the effect of age-friendly outdoor spaces with specialised outdoor exercise equipment on older people’s physical activity and wellbeing in six Victorian municipalities (local governments/councils). Each council will undergo four stages (site construction and development, promotion and marketing, capacity building and training, evaluation and sustainability). Several activities and methods will be employed from stage one through stage four to evaluate the potential impact of the age-friendly outdoor spaces on physical activity and wellbeing and will comprise the following elements: site observation and equipment utilisation, face to face intercept surveys, development of an online access monitor and community building activities.

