We have been undertaking research for the past several years involving a specialised outdoor multimodal exercise equipment, the Seniors Exercise Park, and developed and tested an outdoor physical and social activity program for older people in the community. The Seniors Exercise Park integrates multimodal exercise stations that target balance (unstable/uneven surfaces), strength, flexibility and functional movements, designed for use by older people. Building on a Randomised Controlled Trial [10, 11], our work has expanded into public community settings involving the installation of the specialised equipment in multiple communities (The ENJOY project). Participation in the ENJOY program resulted in various health benefits including improved physical function and wellbeing as well as sustained engagement in physical activity, perceived enjoyment and enhanced socialisation for older people [12, 13].

The outcomes achieved so far from the ENJOY project suggest that the Seniors Exercise Park is effective in improving older people’s physical function and wellbeing and can be an important public health infrastructure investment in promoting physical activity for older people. It was also evident that working with local governments and community in partnership can play a major role in promoting community health through physical activity [14]. Wider implementation of this initiative to include more specialised equipment in the community and hence further local governments’ engagement can potentially have greater public health benefits. In addition, effective communication, strategic planning and community and older people engagement approaches are important for successful implementation [14]. The ENJOY MAP for HEALTH builds on our previous work and the lessons learnt to better improve the built environment to promote physical activity for older people. The ENJOY MAP for HEALTH aims to evaluate the impact of the Seniors Exercise Park installation and associated capacity building activities on older people’s park visitation, park-based physical activity and delivery of community physical activity programs. The ENJOY MAP for HEALTH will involve the installation of the specialised Seniors Exercise Park equipment supported by promotion and community capacity building activities in six municipalities in Victoria, Australia.

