**Fig. 1 Fig1:**
[figure not shown]
Project’s stages for each site

To address the study aims, multiple methodologies will be employed throughout the project at each site (estimated 18 months process within each site) to evaluate the impact of site refurbishment and equipment installation on park visitation and physical activity engagement and participation of older people. These will include direct observations of park users, onsite intercept surveys with park users, online access monitor platform (using an online app, *ENJOY-ME-APP’*), and review of the physical activity program offered by the participating partners and or the respective local health/leisure providers. Please refer to Fig. 2 for the project’s timeline and activities.

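### The aim includes an effect on delivery of community physical activity programs, but the audit takes one late count of equipment-based programs, with no baseline

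*Protocol article*

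**What the plan says.** The Abstract (Background) lists three targets on which the effect of installation and capacity building is to be evaluated: "park visitation, park-based physical activity by older people and delivery of community physical activity programs". The main Background section repeats the aim as an impact, again including "park-based physical activity and delivery of community physical activity programs". Neither restricts the third target to programs that use the equipment. The Abstract (Method) names the design: "This study is a quasi-experimental (natural experiment) with pre and post study design".

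Measurement of the third target is set out under Review and audit of physical activity programs. Its content is the "type and number of physical activity programs for older people using the Seniors Exercise Park", supplied by the council. Its timing is "This information will be collected in the last stage of each site between 15 and 18 months". Methods and design describes an "estimated 18 months process within each site", so this is the end of the process.

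Methods and design also lists the review among the study methods. There it covers programs offered by the partners or local health and leisure providers, with no restriction to the equipment and no timing.

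**The concern.** A pre and post design estimates an effect by comparing the same quantity before and after. For program delivery, the article describes only an after measurement, and of a narrower quantity than the aim names. Programs using the equipment cannot exist at a site before it is installed, so their count carries no information about what was on offer beforehand. A class moved from a hall to the park is counted like a class that did not exist before.

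The risk lies in interpretation. If the final count is reported against the aim as worded, a reader may take it as growth in provision for older people when the data cannot distinguish growth from relocation. A baseline not collected cannot be restored by analysis later, except where councils hold records.

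**Working it through.** The article gives no figure to reproduce here. The check sets the sections side by side and asks what the audit can identify.

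**Timing of each target in the aim**

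| Target | Before construction | Afterwards | Section |
|---|---|---|---|
| Park visitation and park-based activity (observation) | Yes | One month after opening; 12 months after baseline | Park observation and Seniors Exercise Park equipment usage |
| Visitors' own reports (survey) | Yes | 12 months | Intercept survey with visitors |
| Program delivery | None stated | Once, months 15–18 | Review and audit of physical activity programs |

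Only program delivery lacks a before measurement.

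**What the count identifies**

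Let E be the number of programs for older people that use the equipment, and O the number of other such programs. The before–after change in delivery is

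(E_post + O_post) − (E_pre + O_pre).

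- E_pre = 0, because the equipment is not yet there.
- O_pre and O_post are not collected under the audit section.
- Only E_post is observed.

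The change is therefore E_post + (O_post − O_pre), with the bracket unknown. If E_post = k and r of these were moved from another venue (0 ≤ r ≤ k), those programs contribute a net gain of k − r, anywhere from 0 to k. Any other openings or closures add a further unrecorded change.

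**Illustration (assumed numbers)**

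A council has 5 programs before installation, and 2 use the equipment at 15–18 months.

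| Scenario | E_post | O_post | Total after | Change from 5 |
|---|---|---|---|---|
| Both new, the other 5 continue | 2 | 5 | 7 | +2 |
| Both relocated, the other 3 continue | 2 | 3 | 5 | 0 |
| Both relocated, one of the other 3 closes | 2 | 2 | 4 | −1 |

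The audit records 2 in all three rows.

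**Does other text close the gap?**

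- The broader wording in Methods and design would bring O_post into scope if followed, but it gives no baseline, so O_pre stays unknown.
- Statistical analysis names counts of people observed, walking or active as the modelled outcomes. It names no analysis of program delivery.
- Relocation is plausible: Site activation says the project will engage local health care and leisure providers to deliver programs on the equipment.

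**The case against.** The strongest reply is that this element was only ever meant to describe uptake. Site activation states the long-term intent that providers develop and deliver programs on the equipment, and the audit sits in the final evaluation and sustainability stage. On that reading the prior value is known to be zero, a single late count is correctly timed, and total provision is not an outcome. This stands as a defence of the count as a measure of uptake. It does not match the aim, which twice promises an effect or impact on delivery of community programs.

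A reader might go further and infer that the third target can only come out positive, or that every site will show zero against some positive number. The article does not support that. A site may record no programs, so the audit can show that uptake failed. No zero-to-count comparison is planned either: the hypothesis concerns older visitors only.

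Two more replies deserve an answer. Fig. 2 is not shown, but the audit section cites it for the 15–18 month timing, so a baseline audit there is unlikely. Whether the audit form marks programs as new or relocated could be left to a fuller document. The scope and timing are different, because the article fixes them itself.

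Finally, a before–after list would still not prove causation. There are no control sites, and COVID19 risks mitigation anticipates restrictions that could themselves change provision. That is correct, and it limits how the result may be reported.

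**Conclusion.** The point holds in a limited form. The audit as described measures uptake of equipment-based programs. It cannot show the direction or size of any change in overall provision for older people, nor separate added from relocated programs. One of the three targets in the stated aim is affected. The hypothesis of at least a twofold increase in older visitors is untouched.

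It would be too strong to say that the aim is unattainable on any reading: read narrowly as uptake, the count is valid description. The conclusion rests on taking the aim as worded in the Abstract and Background, and on the text being complete about audit timing. The broader description in Methods and design and the narrower one in the audit section must be reconciled in either case.

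**What to change.** Ask each council's Positive Ageing team (or equivalent) the same question at baseline and at 15–18 months: the number and type of physical activity programs for older people offered by the council and its partner providers. Where baseline has passed, take the earlier figure from council records. In the later list, mark each program using the Seniors Exercise Park as new, relocated or continued. Align the wording in Methods and design with the audit section.

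Report the before–after change descriptively, by site, stating that there are no control sites and that COVID restrictions may have affected it.

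The cost is one added data request per council, six in all, plus the marking of programs in the later list. Provider records may be incomplete, and this should be reported. A full municipal inventory at every venue, with weekly sessions, would be a larger task and is not needed.

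If no baseline can be obtained, restate this part of the aim as describing uptake of equipment-based programs, and draw no conclusion about an effect on community program delivery.

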### Seniors Exercise Park installation and site activation

#### The Seniors Exercise Park equipment installation

The Seniors Exercise Park equipment is outdoor exercise equipment specifically designed for older people to improve strength, balance, joint movements and mobility and function (Fig. 3). It comprises multiple equipment stations that target specific function or movement (upper and lower limb) such as shoulder range of movement, static and dynamic balance, functional movement of walking up/down stairs, sit to stand. Councils will be provided with guidance around suitable flooring/surface (rubber surface or equivalent) and other safety measures for installation [9, 25]. The equipment is located outdoors and safe to use by various age groups (Fig. 3). Our previous multiple projects found the exercise park to be safe for older people (aged 60 years and over and with increased risk of falls) with no serious adverse events [11, 12].

**Fig. 3 Fig3:**
[figure not shown]
The Seniors Exercise Park at Thomas St Reserve, Hampton. The picture was taken by the lead investigator

#### Site activation

This project design and its implementation focus around sustainability. The ENJOY MAP for HEALTH incorporates four stages at each participating site with several strategies embedded to ‘activate a site’ to enable positive effects on physical activity behavior and sustainability: (1) promotion and marketing and (2) capacity building; both including development of resources. These will enable: ongoing promotion of physical activity opportunities, increased usage of the Seniors Exercise Park for community members, increased knowledge and community upskilling, and increased visitation to the park beyond the project completion.Promotion and marketing

All four stages will be enhanced by ongoing communication and branding strategies and activities which will maximise visibility of the participating partners as well as increasing social/community connection. The branding strategy will include, but not be limited to, the design of promotional material to be distributed in online and off line channels such as digital (Facebook, Instagram, website) and physical promotion (banner, posters, flyers) platforms. Community events (official park launch, come-and-try sessions) will also be organised to engage and reach community members.2)Capacity building—upskilling and training– knowledge transfer

Training modules will include training for allied health professionals (Training workshops) and Senior Champions (Train the Trainer).

This will take place in stage two at each site. Relevant resources will be developed to support the workshops and training including on-line resources (video materials) and written educational materials (e.g., manuals).

Training workshops for allied health professionals: A half day training workshop will be delivered at each site for local allied health professionals that will cover safe Seniors Exercise Park use, exercise prescription and program design using the Seniors Exercise Park, incorporating risk management, theoretical and practical sessions.

Train the Trainer module: ENJOY champions: The train to train module aims to train and qualify seniors/community members (older people from the community) to facilitate utilisation of the Seniors Exercise Park for their members/peers, and more widely in the local community. Using this approach maximises community engagement and physical activity participation of the wider community of older people. The ENJOY champions will also be actively involved in project and council events. Train the trainer module will include twice weekly training sessions for 5 weeks as follows: 9 practical training sessions using the Seniors Exercise Park (1.5 hours duration incorporating interactive teaching with hands-on demonstrations) and final theoretical session for 3 hours incorporating risk management, physical activity and healthy lifestyle tips. Adherence will be monitored using participation log.

2 b)Community health care and leisure centre providers engagement

We will work closely with the Positive Ageing and Disability and Community Development teams at each local government council to identify and develop relationships with local health care/leisure providers. This will enable engagement throughout the various project stages including involvement in training, project meetings, and community events. The long term engagement aims for health care and leisure centre providers to actively participate in the development and delivery of a service/program utilising the Seniors Exercise Park for older people.

